**Methods::**

PRIME-KS is a multicountry prospective mixed-methods study with two clinical objectives. Objective 1 is a cross-sectional diagnostic accuracy study comparing SS3D with ruler-based measurement in 50 adults with KS (150 lesions) across sites in Kenya and Uganda. Two clinicians independently measure three lesions per participant using both methods. The primary outcomes are concordance correlation coefficient (CCC) for inter-rater reproducibility, and co-efficient of determination for accuracy. Objective 2 is a non-randomized before-and-after pilot study in 100 patients at three sites, evaluating device usability, acceptability, appropriateness, and feasibility using validated instruments, along with time-and-motion studies and activity-based micro-costing. Prior to these clinical objectives, a formative study used focus group discussions, discrete choice experiments, and human-centered design workshops to refine the SS3D device and protocols with end-user input.

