### Explanation for the choice of comparator {9b}

The comparator is the current standard of care for KS lesion measurement: manual ruler-based assessment using ACTG criteria, which calculates lesion area as the product of the longest perpendicular diameters (Figure 1).^1, 2^ This method was selected because it is the globally recognized standard for KS treatment response assessment used in clinical trials. Comparing SS3D against this established method will determine whether SS3D offers superior reproducibility and accuracy for clinical decision-making.

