### Outcomes {16}

#### Objective 1 (Reproducibility and Accuracy)

##### Primary outcomes:

(1) Concordance correlation coefficient (CCC) for inter-rater reproducibility of KS lesion area measurement. The CCC will be calculated separately for SS3D and for the ruler-based method, based on measurements by two independent clinicians of the same three lesions per participant. The measurement variable is projected lesion area (mm^2^). The method with the higher CCC will be considered the more reproducible. (2) Coefficient of determination (R-squared) for each measurement method, assessing the proportion of variation attributable to true lesion size versus random measurement error.

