### Statistical methods

Statistical methods for primary and secondary outcomes {27a}

#### Objective 1

We will plot a graph for each measurement method. Each graph’s x-axis will represent measurements from clinician 1 and y-axis will represent measurements from clinician 2. For each graph, we will calculate the concordance correlation coefficient (CCC) and coefficient of determination (R-squared). The CCC measures reproducibility (agreement) between clinicians for each method. The method with the higher CCC will be considered the more reproducible, and the method with R-squared closer to 1 will be considered the more accurate. We will also visualize agreement between methods graphically using Bland-Altman plots, and report the mean difference and 95% limits of agreement. To provide a more robust assessment, we will also report mean absolute error and root mean square error to capture the magnitude of differences between methods.

#### Objective 2

System Usability Scale (SUS) scores will be computed following standard scoring procedures (score contributions from items summed and multiplied by 2.5, yielding a score range of 0 to 100). Device usability will further be normalized to generate percentile ranks and graded as either acceptable (score above 68), marginal, or not acceptable. AIM, IAM, and FIM scores will be presented as means, standard deviations, and ranges. Qualitative data collected from semi-structured interviews will be transcribed, coded, and thematically analyzed to identify sub-themes and themes related to SkinScan3D implementation in routine clinical settings. Data triangulation will be applied to cross-validate findings from interviews and direct observation to ensure rigor and validity of the qualitative analysis.

For the cost analysis, we will summarize data to estimate the total program cost of SS3D per patient and per visit, excluding research costs. Costs will be broken down by the categories in Table 2 to identify key cost drivers.

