## Discussion

PRIME-KS will provide the first rigorous evaluation of a 3D imaging device for monitoring KS treatment response in routine clinical settings. The study addresses a critical gap in KS care: the absence of a simple, objective, and affordable tool for treatment monitoring that can function effectively, including in resource-constrained settings.

This study provides a unique participatory approach to device development from all stakeholders, ensuring that the SS3D device and protocols are contextually appropriate, acceptable, and designed with the input of the people who will use and benefit from the technology. The formative study activities described under Patient and Public Involvement directly shaped the intervention prior to clinical evaluation, providing a blueprint for participatory approaches to medical device design and implementation in low- and middle-income countries.

Several design considerations merit discussion. The paired within-participant design of Objective 1, in which two clinicians independently measure the same lesions using both methods, is a strength that allows direct comparison of reproducibility while controlling for patient-level variation. The before-and-after design of Objective 2 was chosen over a randomized design because the goal is to characterize the implementation profile of SS3D (usability, acceptability, cost) rather than to demonstrate efficacy; a non-randomized design is appropriate for this purpose and is more feasible given the cluster-level nature of the intervention.

Potential limitations include the lack of a true gold standard for KS lesion measurement. We compare SS3D against the current standard of care rather than against a reference standard such as optical coherence tomography, which is impractical in field settings. Another limitation is that the before-and-after design of Objective 2 is subject to temporal confounding; however, our primary interest is in the implementation profile of the device, for which this design is appropriate. There are also potential challenges of users not fully understanding the technology since it is new, which may yield inappropriate responses during initial implementation; the formative co-creation with potential users, structured training protocol, and think-aloud usability testing are designed to mitigate this.

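### Objective 1 ranks the methods on accuracy by an R-squared between two clinicians, which measures precision and cannot detect an error both clinicians share

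*Protocol article*

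**What the plan says.** Objective 1 has two primary outcomes. The first is the concordance correlation coefficient (CCC) between clinicians. The second is R-squared, which the Abstract describes as "co-efficient of determination for accuracy" and Outcomes {16} explains as "assessing the proportion of variation attributable to true lesion size versus random measurement error". The measured variable is projected lesion area in mm².

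Statistical methods {27a} fixes how R-squared is obtained. There is one graph per method, on which the "x-axis will represent measurements from clinician 1 and y-axis will represent measurements from clinician 2". CCC and R-squared are both taken from that graph. The decision rule is that "the method with R-squared closer to 1 will be considered the more accurate".

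Section {9b} states the purpose: "Comparing SS3D against this established method will determine whether SS3D offers superior reproducibility and accuracy for clinical decision-making". The Discussion concedes: "Potential limitations include the lack of a true gold standard for KS lesion measurement". Sections {19} and {27a} add Bland-Altman plots, mean absolute error (MAE) and root mean square error (RMSE), described as differences between the two methods. Section {5} says the analysis plan is integrated into {27a} to {27d}, so the rule stands as written there.

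**The concern.** Accuracy is closeness to the true area. The graph that yields R-squared carries two readings by the same method and no true or reference area. If a method reads every lesion too large or too small in the same way for both clinicians, the points still lie close to a line and R-squared stays high. The rule nevertheless returns a verdict on accuracy.

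One of Objective 1's two primary outcomes therefore cannot answer its stated question. The protocol's closing discussion attaches consequences to superior accuracy, including earlier decisions on chemotherapy, so the label matters to how results will be read.

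**Working it through.** **The plan's own figure.** Table 1 gives the only precision calculation for Objective 1, and it concerns the CCC. With tanh(atanh(CCC) ± 1.96/√(n − 3)) and n = 150, 1.96/√147 = 0.162.
- CCC 0.8: tanh(1.099 ± 0.162) = 0.734 to 0.851 (Table 1: 0.73 to 0.85).
- CCC 0.9: tanh(1.472 ± 0.162) = 0.864 to 0.927 (Table 1: 0.86 to 0.93).

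Table 1 reproduces. It gives nothing for R-squared or accuracy.

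**What R-squared responds to (exact, no assumption).** R-squared here is the squared Pearson correlation of clinician 1's readings x with clinician 2's readings y.
- Constant error c shared by both: corr(x + c, y + c) = corr(x, y).
- Proportional error k > 0 shared by both: corr(kx, ky) = corr(x, y).

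In one simulated set of 150 lesions, adding 50 or 100 mm² to both readings, or multiplying both by 0.5, 4/π or 2, left R-squared at 0.897 and CCC at 0.947.

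**Relation to the other primary outcome.** CCC = r × C_b, where C_b penalises differences in mean and variance between the two clinicians. R-squared is r², the precision part alone. In simulation, adding 100 mm² to one clinician only left R-squared at 0.927 while CCC fell from 0.963 to 0.798. R-squared thus misses even a bias between clinicians.

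**The ruler in the protocol's own terms.** The ruler area is d1 × d2. An ellipse with those axes has area π·d1·d2/4, so the ratio is 4/π = 1.273, a 27% excess. Both clinicians apply the same formula, so R-squared cannot register it.

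**When the rule picks the wrong method.** Suppose SS3D reads true area with independent clinician error of SD e_S, the ruler reads k = 4/π times true area with error SD e_R, and true areas have SD σ. Then:

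R-squared(SS3D) = [σ²/(σ² + e_S²)]²; R-squared(ruler) = [k²σ²/(k²σ² + e_R²)]².

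The ruler's value is larger whenever e_R < 1.273 × e_S, although every ruler area is 27% too large.

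Illustration, with assumptions that are not in the protocol: lognormal true areas, median 150 mm², log-SD 0.7 (mean about 192, σ² about 23,200), and e_S = 30 mm².

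| Method | R-squared |
|---|---|
| SS3D, SD 30 | (23,200/24,100)² = 0.927 |
| Ruler, SD 30 | (37,610/38,510)² = 0.954 |
| Ruler, SD 38.2 (= 1.273 × 30) | 0.927, a tie |
| Ruler, SD 40 | (37,610/39,210)² = 0.920 |

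At SD 30 for both, the RMSE to truth of the average of the two readings is 21 mm² for SS3D and 70 mm² for the ruler. At 150 lesions the rule named the ruler more accurate in 99.8% of 4,000 simulated studies. At ruler SD 40 the expected order reverses. The verdict turns on scatter relative to spread; bias never counts against a method.

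**The gloss in {16}.** For two parallel readings, the share of variance due to true size is r, not r². A share of 0.90 gives R-squared 0.81. The gloss also mentions only random error, whereas accuracy includes systematic error.

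**The case against.** The strongest defence is that the protocol foresees overinterpretation. Section {19} complements R-squared with Bland-Altman plots for systematic bias, MAE and RMSE, which it describes as capturing accuracy more directly. A large shared error in one method would probably appear as a mean difference between SS3D and ruler, and would be reported. That stands. But these are differences between two methods, neither of which is truth. They show disagreement without showing its source, they are secondary, and the R-squared rule remains unaltered beside them.

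The study is also declared exploratory and discloses the missing gold standard. Both are true, but the disclosure contradicts the accuracy rule and does not repair it. True lesion size does influence R-squared, because its variation is the signal the clinicians share; its level does not.

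Three stronger readings are tempting and are not supported:
- That a method both clinicians misread will be declared more accurate. A shared shift leaves R-squared where it was, so the biased method gains nothing from it and loses if its relative scatter is larger.
- That the rule favours SS3D by construction because its area is automated. The protocol nowhere says that SS3D errors repeat across operators.
- That a biased SS3D would wrongly beat the ruler. Suppose SS3D reads 25% low with 5% random error and the ruler reads 1.273 times true area with 15% random error. Relative RMSE is √(0.25² + (0.75 × 0.05)²) = 25.3% against √(0.273² + (1.273 × 0.15)²), about 33%. With its smaller relative scatter SS3D would be preferred, and it would be the closer method. The rule would be right by luck.

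**Conclusion.** The concern holds in this form: R-squared between clinicians is a precision measure that {27a} uses as an accuracy ranking, and no quantity in Objective 1 measures accuracy. The invariance to shared constant or proportional error is exact. The 27% figure assumes round or oval lesions; irregular ones will differ. The break-even factor of 1.273 assumes an SS3D that reads true area and independent clinician errors. The R-squared values, RMSEs and the 99.8% rest on assumed lesion sizes and error SDs and only illustrate that a wrong verdict is possible. They do not predict which method this trial will favour.

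The CCC outcome and Table 1 are unaffected. The closing statement about superior accuracy is conditional, so the protocol does not claim the result in advance. What is wrong is that the condition would be judged by a statistic that cannot test it.

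**What to change.** - **Outcomes {16} and Abstract (Methods):** rename primary outcome 2 as inter-clinician association (precision), and remove or correct the gloss about true lesion size.
- **Statistical methods {27a}:** delete the rule that "the method with R-squared closer to 1 will be considered the more accurate". Report R-squared alongside CCC without an accuracy verdict.
- **Abstract (Background and Methods), Objective 1 in {10}, {9b}, {12} and Discussion:** limit the conclusion to inter-rater reproducibility and between-method agreement, and state that accuracy is not estimated because there is no reference area.
- **Sample size {19}:** describe Bland-Altman, MAE and RMSE as measures of between-method agreement, not of accuracy.

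No new data are needed. Because a primary outcome is relabelled, the change probably counts as substantive under {31}, with ethics submissions and registry updates. Uganda began recruiting on 1 April 2026, Kenya has not begun, and completion is expected in Q4 2027, so it can be made well before analysis. The scientific cost is a narrower claim: reproducibility and agreement without accuracy.

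If the accuracy claim is to be kept, a reference area is needed, for example objects of known area or an independent tracing, with bias and RMSE against it. That means extra data collection.

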## Introduction

### Background and rationale {9a}

Traditional monitoring of treatment response for Kaposi sarcoma (KS) relies upon user observation and measurement of changes in lesion dimensions based on user observation of color contrast between lesion and normal skin. This may miss subtle changes in lesion pigment that may not be readily apparent, especially in patients with skin of color. In addition, this method suffers from inter-observer variability. Three-dimensional (3D) imaging removes user subjectivity and mitigates problems with identifying and characterizing KS lesion changes on patients by providing an independent measurement of cutaneous tumor volume based on 3D shape with precise calculation of lesion area, instead of the more problematic color contrast and perpendicular lengths.

There is an unmet need to develop simple, accurate, and less burdensome tools for monitoring KS treatment. Currently, response to KS treatment is assessed using manual ruler-based measurements defined by the AIDS Clinical Trial Group (ACTG) Oncology Committee. ^1, 2^ This method involves time-consuming and tedious manual measurement of multiple lesions using a ruler with millimeter precision, leading to inter- and intra-observer variation and failing to capture the true geometric area (Figure 1).

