##### Comparator (ruler-based measurement):

Participants will have three discrete skin lesions measured using the standard ACTG method, in which lesion area is determined as the product of the longest perpendicular diameters using a ruler with millimeter precision (Figure 1).^1, 2^ This is the current global standard for KS response assessment in clinical trials.

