#### Objective 1 measurements

For each participant we will collect demographic and clinical data regarding KS diagnosis and extent of disease. Thereafter, two clinicians will each measure three lesions using both the manual ruler-based method (standard of care) and SS3D. Standard of care measurement: Participants will have three discrete skin lesions measured, with lesion area determined by ACTG criteria utilizing the product of longest perpendicular diameters. Participants will also have five 3D snapshots of each of the three target lesions taken, measuring lesion area automatically using SS3D AI.

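### The secondary between-method metrics set a ruler product d1 × d2 against a device-computed area, so the mm² bias carries a built-in geometric offset (about 27% for round or oval lesions)

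*Protocol article*

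**What the plan says.** Under Comparator {15a}, "lesion area is determined as the product of the longest perpendicular diameters using a ruler with millimeter precision". Objective 1 measurements {25a} repeats this: "lesion area determined by ACTG criteria utilizing the product of longest perpendicular diameters". The Figure 1 legend gives the same product and shows oval, round and irregular outlines. No shape factor is applied anywhere.

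The same measurements section describes the device as "measuring lesion area automatically using SS3D AI". Background {9a} presents this as "precise calculation of lesion area, instead of the more problematic color contrast and perpendicular lengths", and faults the ruler method for "failing to capture the true geometric area". The primary outcomes in {16} nevertheless name one variable, projected lesion area in mm², for both methods.

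Statistical methods {27a} says the team will "visualize agreement between methods graphically using Bland-Altman plots, and report the mean difference and 95% limits of agreement", and that MAE and RMSE will describe the size of the differences between methods. Outcomes {16} lists all of these as secondary. Sample size {19} gives them a stronger reading: they are to capture accuracy more directly than R-squared does, and the Bland-Altman plots are to show systematic bias. Section {5} says the statistical analysis plan is integrated in {27a} to {27d}. Those sections mention no conversion, no ratio scale and no d1 × d2 output from SS3D.

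**The concern.** A Bland-Altman difference tells us about measurement error only if both methods aim at the same quantity. Here one aims at the area inside the lesion outline. The other reports the area of a rectangle whose sides are the two diameters. Part of the mean difference is then fixed by geometry before any patient is measured.

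This matters because the primary CCC and R-squared compare clinician 1 with clinician 2 within each method. The Bland-Altman, MAE and RMSE results are the plan's direct numerical comparison of SS3D with the ruler. If the difference is read as accuracy, an error-free SS3D looks biased low. A device that draws round or oval lesions too large by the same factor looks unbiased.

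**Working it through.** **The plan's own figure.** The protocol gives no expected between-method difference. Its only computed figure for Objective 1 is Table 1, on the CCC. That table reproduces with tanh(atanh(CCC) ± 1.96/√(n − 2)). At 150 lesions this gives 0.734 to 0.851 for CCC 0.8 and 0.865 to 0.927 for CCC 0.9, against the stated 0.73 to 0.85 and 0.86 to 0.93. Table 1 does not bear on the between-method metrics.

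**Ratio for round and oval outlines** (Figure 1, A and B).
- Ruler value: d1 × d2. Enclosed area: (π/4) × d1 × d2.
- Ruler / area = 4/π = 1.273, at any elongation.
- The gap is 1.273 − 1 = 27.3% of the true area, 1 − π/4 = 21.5% of the ruler value, and 0.2146 / [(1 + 0.7854)/2] = 24.0% of the Bland-Altman mean of the two.

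**Growth with size, no measurement error.**
- 10 mm round lesion: 100 v 78.5 mm², difference 21.5.
- 20 mm round lesion: 400 v 314.2 mm², difference 85.8.

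For error-free round or oval lesions the difference is an exact multiple of the mean, so their correlation is 1.0.

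**Other outlines.** The longest diameter, longest perpendicular chord and area were measured on constructed shapes.
- 10:1 rectangle: excess 1%.
- 3:1 rectangle: 3.162 × 1.054 = 3.333 v 3, excess 11%.
- Square: 1.414 × 1.414 = 2 v 1, excess 100%.
- 100 simulated irregular outlines (assumed shapes): median excess 35%, 95% range 26% to 53%.

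**Size in mm².** The documents give no lesion-size distribution, so both of these are assumptions. Both use elliptical lesions and error-free methods.

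| Assumption | Mean difference = MAE | RMSE | Limits of agreement |
|---|---|---|---|
| d1 lognormal, median 10 mm, log-SD 0.4; d2/d1 uniform 0.5 to 1 | 22.1 | 31.0 | −20.6 to 64.8 |
| Area lognormal, median 150 mm², log-SD 0.8 | 56.4 | 77.7 | −48 to 161 |

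Second row in closed form: mean area = 150 × exp(0.32) = 206.6, and 0.2732 × 206.6 = 56.4. Root mean square area = 150 × exp(0.64) = 284.5, and 0.2732 × 284.5 = 77.7. The SD of the differences is √(77.7² − 56.4²) ≈ 53.4, so the limits are 56.4 ± 1.96 × 53.4.

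These two rows are examples, not bounds. Taking d1 with median 20 mm and log-SD 0.5 gives a mean difference of 106 mm².

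**After matching.** Multiplying the ruler product by π/4 makes mean difference, MAE and RMSE all 0 for error-free round or oval lesions. For the simulated irregular outlines the residual ratio is 1.346 × 0.785 = 1.06 at the median, with a 95% range of about 0.99 to 1.20.

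**Primary outcomes.** A constant factor applied to both clinicians' values cancels from the CCC and R-squared. A simulated CCC was 0.9054 both before and after scaling by 4/π.

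**The case against.** The comparator is deliberately the ACTG product as used in trials ({9b}), and its failure to capture true area is part of the rationale. How far the ACTG number departs from a measured area is therefore a fair descriptive question, and the raw difference answers it. This stands, and it is a reason to keep the raw comparison on display. It does not support reading that difference as accuracy or systematic bias, as {19} does, because the shape component is never separated from rater, device or segmentation error.

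The affected metrics are also secondary, no decision rule uses them, and the study calls itself exploratory. {27a} judges reproducibility by CCC and accuracy by R-squared. This stands too, and it limits the severity.

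The Discussion does concede that no gold standard exists. That concerns the lack of a reference method. It does not disclose that the two methods report different quantities.

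A reader might infer that the whole reported bias is a geometric artefact, or that the metrics cannot speak to agreement at all. The documents do not support either. Real measurement error adds to the offset in an amount that the protocol does not give, and a Bland-Altman plot would show the offset as a trend with size.

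**Conclusion.** The point holds for the secondary between-method metrics. For round and oval lesions the offset is exactly 4/π, about 27% of true area, and rests on geometry alone. It should not be quoted for all lesions: Figure 1 includes irregular ones, where the excess depends on shape and the range shown above rests on assumed outlines. The mm² figures (bias about 22 to 56, RMSE about 31 to 78) rest wholly on assumed lesion sizes.

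The mean difference, limits of agreement, MAE and RMSE in mm² are confounded with this component and cannot be read directly as accuracy. It would be wrong to infer that the primary reproducibility comparison is compromised, since each method's inter-rater CCC and R-squared are unchanged. Severity: should-fix, secondary outcome.

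**What to change.** In {27a}, and in the sentence in {19} that interprets these metrics:

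1. For between-method metrics, compare matched quantities. Multiply the ruler product by π/4, or have SS3D also output d1 × d2 from its outline if that is available.
2. Compute MAE and RMSE on the matched quantity.
3. Report Bland-Altman results on the log scale, as a geometric mean ratio with 95% ratio limits of agreement. A proportional offset is then a constant shift (ln 1.273 = 0.24) and no longer widens the limits.
4. Keep the raw ACTG product against SS3D area as a descriptive display. State the expected 4/π offset beside it, and do not describe that raw difference as accuracy or systematic bias.
5. Show results by outline shape (round, oval, irregular), because π/4 is only approximate for irregular lesions. The flat, nodular and plaque strata in {27d} do not serve this purpose.

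The cost is wording and analysis code, plus a classification of outline shape. Design, sample size and primary outcomes do not change. Trial status has recruitment running to Q4 2027, so the change can be made before analysis. The downside is a residual shape error on irregular lesions, which the display by shape will expose.
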